ARCHES (Addressing Reproductive Coercion within Healthcare Settings) is a family planning clinic-based IPV/RC intervention originally developed for use in the U.S. and subsequently adapted for LMIC settings, including Kenya. ARCHES involves training existing family planning providers to (1) educate FP clients about the links between reproductive health concerns and IPV; (2) counsel clients on harm reduction behaviors to reduce risk for IPV and RC; and (3) provide clients with information on violence victimization support and related local services. Implemented within routine family planning clinic visits by existing staff, this intervention is designed to be a sustainable and scalable model to address partner violence, unintended pregnancy, and reproductive coercion among women at elevated risk for all three of these interrelated concerns. The ARCHES model has been shown in cluster randomized controlled trials in the United States and Kenya to reduce experiences of gender-based violence and improve reproductive health outcomes [9–11].

In Kenya, an initial matched-pair control trial among 659 women and girls ages 15–49 years seeking FP services from six clinics in Nairobi demonstrated that ARCHES, relative to standard-of-care FP counseling and provision, decreased the odds of leaving the clinic without a modern FP method, improved attitudes regarding RC, and increased awareness of IPV support services. Providers implemented ARCHES with high fidelity (> 80%) [11], and qualitative data from clients and providers showed high feasibility and acceptability to both parties [12, 13]. Based on this evidence and need to address high rates of GBV among FP clients, the Kenya MOH has committed to scaling ARCHES to government health facilities across Kenya via a county-by-county approach, starting in Uasin Gishu county. In this study, the research teams at the University of California, San Diego (UCSD) and Population Council Kenya are partnering with the Kenya Ministry of Health (MOH) to adapt the model to government health facilities, and then pilot, scale and evaluate the model in such health facilities in a single county, Uasin Gishu, to demonstrate effectiveness of the adapted ARCHES model prior to rolling out the model to all counties nationally.

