## Methods/design

### Design overview

We will use a mixed methods approach to evaluate ARCHES as adapted and implemented by the Kenya MOH in government health facilities in Uasin Gishu county, Kenya. We will conduct a cluster-randomized controlled trial (cRCT) with stratified randomization based on facility type and urban/rural location to evaluate the effectiveness of the adapted ARCHES intervention on unintended pregnancy 6-months post-intervention (see Additional File 1 for items from the WHO Trial Registration Data Set). This cRCT will include 24 randomly selected health facilities (total n = 3540 female clients seeking FP care at 24 facilities; facilities are randomly assigned to either intervention or control conditions, 12 facilities per condition) in Uasin Gishu county, Kenya. Data collection from clients (women and girls aged 15–49 seeking FP services from the 24 selected health facilities) will include a baseline survey (immediately prior to receiving care at the health facility), a post-visit or exit survey (at facility immediately after receiving care), and a 6-month follow up survey (Fig. 1). A sub sample of women and girls (n = 36) who received the intervention will also be invited for 3-month follow-up interviews to understand acceptability to clients. To evaluate provider training, we will conduct: 1) pre-training, post-training, 3-month, and 6-month follow-up post-training surveys from all ARCHES trained FP providers (n ~ 60), and semi-structured interviews 3-months post-training (n = 10) and one focus group discussion (FGD) 6-months post-training (n = 1, 6–8 participants) among these providers.

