
#### Control condition

The control condition utilizes an active comparator, and health facilities assigned to the control group will implement standard contraceptive counseling using the BCS +. As mentioned above, the BCS + was adopted by the Kenya MOH as the standard contraceptive counseling protocol in the country, but most public sector providers have not been trained on the BCS + . As a result, the study will train existing contraceptive providers in the control group facilities on the MOH’s contraceptive training package, which will be identical to the six-day training received by intervention group providers except that content on RC and IPV will be removed and the original BCS + counseling algorithm will be used. The training will include use of a control version of the companion mobile application that guides providers through the standard BCS + counseling protocol (without ARCHES content integrated). Similar to the intervention group, control group providers will receive post-training mentorship after returning to their health facilities.

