### Allocation

A total of 24 government health facilities in Uasin Gishu county were randomly selected for study participation. This cluster-randomized controlled trial used parallel assignment to two arms: (1) the intervention arm will implement the ARCHES intervention integrated in the BCS + counseling strategy, and (2) the control arm will implement standard contraceptive care using the BCS + approach. Researchers at UCSD compiled a list of the 24 facilities and stratified based on facility type (hospital, health center, or dispensary) and urban or rural location, and used SAS to generate random numbers to randomize an equal number of facilities to the intervention and control groups within these strata. All FP clients enrolled in facilities assigned to the intervention group are considered intervention group participants, and all FP clients enrolled in facilities assigned to the control group are considered control group participants.

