### Data analysis

Quantitative analyses to evaluate the effectiveness of ARCHES will use an intent-to-treat approach and assess the primary outcome using a multilevel mixed effects generalized linear regression model with logistic regression specifications for the binary outcome, accounting for facility-level clustering. For secondary outcomes, both single timepoint and difference-in-differences analyses will be used to compare treatment to controls, testing for an interaction between time and treatment. Difference-in-differences analyses will consider clustering within health facilities using nested random effects specifications due to repeated measurements over time of individuals nested within health facilities. Analyses will adjust for potentially relevant covariates measured at each time point. In addition to intent-to-treat analyses, we will conduct as-treated analyses to measure the effectiveness of the intervention among those who received ARCHES counseling compared to those who did not. We will also run exploratory analyses segregated by age group (age 15–24 and 25–49).

Survey items for the provider training evaluation will be tabulated and Pearson chi-square tests or T-tests (as appropriate for the outcome) at alpha < 0.05 will be used to compare responses to each item at pre-training and follow-up. For those with significant results, regression models accounting for health facility-level clustering will be used to assess the overall training effect on each outcome.

Missing client and provider data will be assessed for systematic differences between participants with missing and complete data. If systematic differences are observed, multiple imputation of missing data will be used to reduce bias.

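### The supplementary as-treated comparison is not protected by randomisation and can be biased in either direction; a complier-average effect based on facility assignment suits the recipient question better

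*Protocol article*

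**What the plan says.** The Data analysis section makes intent-to-treat the main approach: the evaluation "will use an intent-to-treat approach and assess the primary outcome using a multilevel mixed effects generalized linear regression model", with allowance for facility clustering. It then adds a second analysis, stating that "we will conduct as-treated analyses to measure the effectiveness of the intervention among those who received ARCHES counseling", with those who did not receive it as the comparison group. Only the age-group analyses in the next sentence are called exploratory. On adjustment, the section says "Analyses will adjust for potentially relevant covariates measured at each time point" and names no covariates.

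Two other sections define who falls into the two groups. Under Allocation, arm follows the facility: "All FP clients enrolled in facilities assigned to the intervention group are considered intervention group participants". Under Control condition, control providers get the same training package "except that content on RC and IPV will be removed". Recipients of ARCHES should therefore come essentially only from intervention facilities.

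**The concern.** The only randomised comparison is between facilities (Design overview: "facilities are randomly assigned to either intervention or control conditions, 12 facilities per condition"). Sorting women by receipt splits the intervention arm after randomisation. The women at intervention facilities who missed ARCHES are moved into the comparator with all the controls. If missing ARCHES goes with higher or lower pregnancy risk for any other reason, the contrast mixes that difference with the effect of counselling.

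The stated purpose makes this matter. The analysis is described as measuring effectiveness, and the Dissemination section says the results will inform whether and how the model is scaled to other counties. A recipient estimate printed beside a diluted intent-to-treat estimate invites the reading that it is the undiluted version of the same effect. It need not be.

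**Working it through.** **Inputs from the protocol article.** From Power and sample size: risk 3.13% under standard care and 1.72% with ARCHES, 1770 women per arm, 80% retention. Evaluable women per arm = 1770 × 0.80 = 1416.

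**Check of the plan's own figure.** (0.0172/0.9828) / (0.0313/0.9687) = 0.542, which agrees with the stated 0.54.

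**Assumptions, not in the documents.** c is the share of intervention women who receive ARCHES: 80%, range 60% to 90%. The only pointer is provider fidelity above 80% in the earlier Nairobi trial (Background), which is a different quantity. k is the risk in non-recipients divided by the risk in recipients within the intervention arm: 0.5 to 3.

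**Formulas under no true effect.** Both arms have 3.13% risk overall.

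- Recipients' risk: r = 3.13% / (c + (1 − c)k)
- Risk in intervention-arm non-recipients: kr
- Risk in the pooled comparator: q = [1416 × 3.13% + 1416(1 − c) × kr] / [1416 + 1416(1 − c)]
- As-treated odds ratio: [r/(1 − r)] / [q/(1 − q)]

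**Worked case, c = 0.80 and k = 2.** r = 3.13%/1.2 = 2.61% and kr = 5.22%. The comparator has 1416 + 283.2 = 1699.2 women, and q = (1416 × 3.13% + 283.2 × 5.22%)/1699.2 = 3.48%. The odds ratio is 0.0268/0.0360 = 0.74.

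Crude as-treated odds ratio when the true effect is nil:

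| Delivery c | k = 0.5 | k = 1 | k = 1.5 | k = 2 | k = 3 |
|---|---|---|---|---|---|
| 60% | 1.42 | 1.00 | 0.77 | 0.63 | 0.46 |
| 80% | 1.21 | 1.00 | 0.85 | 0.74 | 0.59 |
| 90% | 1.10 | 1.00 | 0.91 | 0.84 | 0.73 |

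**Complier-average effect on the same inputs.** In the worked case the intervention-arm risk is 0.80 × 2.61% + 0.20 × 5.22% = 3.13%. The intent-to-treat difference is 0, and 0/0.80 = 0. The same holds in every cell of the table.

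**With a facility random intercept.** The mixed model planned for the primary outcome was fitted to the as-treated contrast in 400 simulated null trials per scenario (24 facilities, mean 118 evaluable women each, cluster-size variation 50%, intra-class correlation 0.1 taken on the latent logistic scale, 80% delivery, no covariates). For k = 1.5, 2 and 3 the median as-treated odds ratio was 0.74, 0.60 and 0.42. A false benefit was declared at alpha 0.15 in 35%, 63% and 91% of trials. The odds ratio lies further from 1 than the crude one because the random intercept gives weight to the within-facility contrast between recipients and non-recipients, which here is selection alone. The mean complier-average risk difference in the same data was −0.0005 to −0.0007, with two-sided rejection of 13% to 15%. The 0.15 level is the plan's threshold for the primary outcome; the article gives none for the as-treated result.

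**Where the complier-average effect fails.** It requires that assignment has no effect on women classed as non-recipients. Suppose k = 2, c = 0.80, no effect in recipients, and assignment cuts non-recipients' risk by 25%. The estimate then shifts by (0.20 × 0.25 × 5.22%)/0.80 = 0.33 percentage points in favour of ARCHES; the simulation of this case gave 0.23 points.

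**The case against.** The strongest reply is that this is a supplementary analysis. Intent-to-treat is the stated approach, the sample size and the Ministry of Health's threshold attach to the primary outcome, and no decision rule uses the as-treated result. That stands. A reader might infer that the trial's primary conclusion is at risk; the documents do not support that.

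A reader might also infer that the bias favours ARCHES. The documents do not show this either. They describe no selection mechanism, and Data collection says the services go to all clients at these facilities. The mobile application is expected to improve fidelity (Discussion). If higher-risk women who disclose coercion or violence receive more of the content, the bias runs against ARCHES, as in the k = 0.5 column. With near-complete delivery or k near 1, little bias remains. Adjustment for baseline covariates may reduce it, though it does not restore randomisation, and the figures above are unadjusted.

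The alternative also has limits. It is not free of bias without conditions: ARCHES comprises education, screening, referral and a booklet, so a woman classed as not counselled may still have received part of it. Its test is essentially the intent-to-treat test. It is also tempting to scale the planned difference by delivery, (3.13 − 1.72)/0.80 = 1.76 percentage points. The 1.72% is reported for those receiving ARCHES, so this may correct twice and should not be relied on.

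Lastly, the definition of receipt, the covariates and the model could be left to an analysis plan that is not shown. That is fair for the details. The comparator and the claim of effectiveness, however, are stated in the article.

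**Conclusion.** The point holds for the supplementary analysis. As stated, the as-treated contrast compares groups that were not randomised, and it can show benefit or harm when ARCHES has no effect. At an assumed 80% delivery and no true effect, the crude odds ratio runs from 1.21 (non-recipients at half the risk) to 0.59 (three times the risk), against a design odds ratio of 0.54. These are illustrations: their size and sign rest on delivery and selection figures that the documents do not give. Because non-receipt is essentially one-sided, the complier-average effect is the effect among recipients, which is the question the article poses, provided the exclusion restriction holds. The change is worth making, but the primary result does not depend on it.

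**What to change.** For the effect among recipients, replace the as-treated analysis with a complier-average causal effect, using randomised facility assignment as the instrument for receipt and inference that respects facility clustering. It needs the same receipt variable as the as-treated analysis. Its source in the trial should be named, since exit-survey tracking of fidelity is described only for the pilot.

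State the exclusion restriction. Check it with a sensitivity analysis that counts a woman as a recipient if she received any ARCHES component, including the booklet.

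If the as-treated contrast is kept, label it descriptive and non-randomised and draw no effectiveness claim from it.

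The cost is a change of wording and one further model with its sensitivity analysis. The downsides are a wider interval than the as-treated contrast gives, reliance on the exclusion restriction, and no added power over intent-to-treat.

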### Data collection

After administering informed consent, RAs will complete the baseline survey with FP clients who agree to participate. The baseline survey will measure sociodemographic characteristics and key outcomes for difference-in-differences analysis. After completion of the baseline survey, the FP client will be walked back to the FP counseling waiting room (their previous place in line will be saved by clinic staff). When it is the participant’s turn, they will be seen for their appointment, during which the provider will deliver either the ARCHES intervention (at intervention health facilities) or standard FP counseling (at control health facilities). These services will be provided to all female FP clients at these health facilities regardless of whether they participate in the study. After the FP appointment, all participants will be directed back to the RA in a private room to complete a post-visit (exit) survey, be screened for distress, receive their compensation payment of 500 Kenyan shillings and written referrals, and schedule their six-month follow up visit. RAs will call participants to remind them of the scheduled six-month follow-up and reschedule as needed. On the day of the six-month follow-up visit, participants will return to the health facility or another location of their choosing to complete their follow-up survey. After completing their 6-month follow-up survey, participants will be given 1000 Kenyan shillings. A larger compensation payment will be given at follow-up to cover participant travel costs and to promote retention. All client surveys will be RA-administered and completed on tablets with the survey programmed in Open Data Kit (ODK), which will be programmed to require a response to all questions and other data quality controls such as including range checks for data values.

Providers trained as part of the study will complete a pre-training survey on the first day of training before any content is delivered, a post-training survey on the last day of training, and three-month and six-month follow-up surveys. Providers will not be compensated for their participation. Provider surveys will be self-administered on tablets with the survey pre-programmed in CommCare (Dimagi).

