### Data safety and monitoring plan

Data and safety monitoring of study participants will focus on two major safety aspects: (1) assurance that no harm comes to participants because of research participation and (2) assurance that all data collection from this study maintains the privacy of research participants. Major mechanisms of precaution include the use of confidential and anonymous data. Data from interviews and focus groups (translated transcripts) will include no personal identifiers. Survey data and audio-recordings of semi-structured interviews maintained for this study will only be labeled with unique participant identifiers; no names or other identifiers will be stored with any data collected. Population Council Kenya will maintain a list to link unique participant identifiers with personal identifiers (names, phone number) that will be stored in a secure file location separate from the database; the list will only be used for purposes of follow-up data collection, after which it will be destroyed. For qualitative focus groups and interviews, all physical data collected (i.e., audio files from focus groups and interviews) will be transcribed and translated from Kiswahili or Kalenjin to English without personal identifiers prior to electronic storage, coding, management, and analysis. Original copies of audio files that may include personal identifiers will be destroyed after transcription and translation are completed. Data management for electronic quantitative survey data collected via tablet mobile devices will include no personal identifiers and be assigned a unique study identifier. Survey data will be automatically uploaded and maintained on a secure, encrypted server. Data files will be stored on the secure online server at UCSD, which is backed up every night to minimize the likelihood of lost files. The server will be password protected and only study personnel at UCSD and Population Council will have access to the data. All research staff collecting and translating or transcribing data from this study will sign an agreement in which they agree to maintain absolute confidentiality of all participants within this research project. If any privacy or data security arrangement is violated, either through physical tampering or breach of confidentiality, the individual making the discovery will immediately notify the PIs who report the breach to the IRBs. There are some circumstances in which confidentiality may be breached by the researchers. If the participant directly informs research staff of his/her intentions of homicide or suicide, the researcher will immediately contact authorities (police or mental health) to help address the issue.

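### The provider-training evaluation tests repeated answers from the same providers with an independent-samples chi-square, then models only the items that reach significance

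*Protocol article*

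**What the plan says.** The Design overview plans "6-month follow-up post-training surveys from all ARCHES trained FP providers", about 60 people, together with pre-training, post-training and 3-month surveys. Data collection confirms that these are repeated measurements on the same people: "Providers trained as part of the study will complete a pre-training survey on the first day of training before any content is delivered", followed by "a post-training survey on the last day of training, and three-month and six-month follow-up surveys". The Data safety and monitoring plan adds that "Survey data and audio-recordings of semi-structured interviews maintained for this study will only be labeled with unique participant identifiers", so a provider's surveys appear to be linkable.

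The Data analysis section sets out two steps for these surveys. First, items are tabulated and "Pearson chi-square tests or T-tests (as appropriate for the outcome) at alpha < 0.05 will be used to compare responses to each item" before training and at follow-up. Second, "For those with significant results, regression models accounting for health facility-level clustering will be used to assess the overall training effect on each outcome". For the client outcomes, the same section specifies nested random effects because individuals are measured repeatedly within facilities. It states no equivalent for providers.

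**The concern.** There are two separate faults, and each would stand without the other.

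- **The named test does not fit categorical items.** Pearson chi-square assumes that the pre-training and follow-up answers come from independent samples. Here they come in pairs. When a provider's two answers are positively correlated, the change varies less than the test supposes, so its p-values are too large.
- **Significance decides which items are modelled.** An item must pass the first test at 0.05 before the regression is fitted. Items with a real change can fail to reach the regression. Those that reach it have been selected for a large observed change, so their estimates tend to be too big. The regression is described as handling facility clustering only, so as worded it may also treat one provider's repeated answers as independent.

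With about 60 providers, a weak screen matters. The readings at stake are whether training changed providers' gender-equitable attitudes and their self-efficacy to address violence, which the Abstract lists among the planned assessments.

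**Working it through.** **Inputs from the article.** About 60 ARCHES-trained providers; four surveys; first-step tests at 0.05; regression for significant items only; 12 intervention facilities. The article gives no power calculation, expected change or within-provider correlation for this component, so there is no planned figure to reproduce.

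**Assumptions.** 60 complete pairs, two-sided 0.05, a binary item, a change of 15 or 20 percentage points from 50%, and within-provider correlation (phi) from 0 to 0.6.

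**Step 1: hand check at 50% to 65%, phi = 0.5.**

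- Both positive: p11 = 0.5×0.65 + 0.5×√(0.25×0.2275) = 0.325 + 0.119 = 0.444.
- Discordant cells: 0.5 − 0.444 = 0.056 and 0.65 − 0.444 = 0.206; sum 0.262.
- True SE of the change: √[(0.262 − 0.15²)/60] = 0.063.
- SE assumed by Pearson, pooled proportion 0.575: √(2×0.575×0.425/60) = 0.090. An observed change of 1.96×0.090 = 0.177 is needed.
- Null SE used by McNemar: √(0.262/60) = 0.066. An observed change of 0.129 is needed.
- Pearson power: Φ[(0.15 − 0.177)/0.063] = Φ(−0.43), about 0.33.
- McNemar power: Φ[(0.15 − 0.129)/0.063] = Φ(0.33), about 0.63.

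**Step 2: type I error with no change, 50% at both times, phi = 0.5.** The discordant total is 0.25. The true SE is √(0.25/60) = 0.0645 and Pearson's is √(2×0.25/60) = 0.0913. The real error is 2×[1 − Φ(1.96×0.0913/0.0645)] = 2×[1 − Φ(2.77)], about 0.6%. Simulation gave 0.8%.

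**Step 3: simulation** (20,000 data sets; 2,000 for exact McNemar).

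| Change | phi | Pearson | McNemar | Exact McNemar |
|---|---|---|---|---|
| 50% to 65% | 0 | 39% | 38% | 32% |
| 50% to 65% | 0.3 | 37% | 52% | 42% |
| 50% to 65% | 0.5 | 34% | 64% | 56% |
| 50% to 65% | 0.6 | 32% | 75% | 66% |
| 50% to 70% | 0.3 | 64% | 78% | 69% |
| 50% to 70% | 0.5 | 66% | 90% | 85% |
| 50% to 70% | 0.6 | 68% | 97% | 95% |

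Pearson's true type I error was 5.5% at phi 0, 2.3% at 0.3, 0.8% at 0.5 and 0.4% at 0.6.

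**Step 4: effect of the gate on the estimate.** Take the case in Step 1. Given that an item passes, its mean observed change is D + SE×φ(z)/[1 − Φ(z)], with D = 0.15, SE = 0.063 and z = (threshold − D)/SE.

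- Pearson gate: z = 0.43, giving 0.15 + 0.063×1.09 = 0.219. A true 15-point change averages about 22 points among items that pass.
- McNemar gate: z = −0.33, giving 0.15 + 0.063×0.60 = 0.188, about 19 points.

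Pairing the first-step test reduces the exaggeration but does not remove it. These are observed changes at the gate, before any regression adjustment.

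**Step 5: facility clustering.** Neither first-step test allows for correlation of change between providers in one facility. If the 60 providers are spread evenly over the 12 intervention facilities (5 each), the variance of the mean change is multiplied by 1 + 4×ICC. In Step 2, Pearson overstates the variance by (0.0913/0.0645)² = 2. An ICC of change of 0.25 would cancel that (1 + 4×0.25 = 2). A larger ICC would make the test too liberal. At phi = 0.3 the overstatement is 1/(1 − 0.3) = 1.43, cancelled at an ICC of about 0.11. The article gives no such ICC, so the real error rate is unknown.

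**The case against.** A condensed article may leave the form of the t-test to an analysis plan, and a paired t-test is still a t-test. That stands. A reader might infer that the protocol prescribes unpaired t-tests and so loses power on scale scores as well. The text does not say so. If they were unpaired, a 0.3 SD change at correlation 0.5 would be detected with 33% power against 63% paired, but that figure is conditional and is not part of the finding.

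Other stronger readings also go too far.

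- *Real training effects will be lost.* This depends on correlation and effect size, which the article does not give. At zero correlation there is no loss.
- *Only significant items will be reported.* The plan tabulates and tests every item. The gate governs only which items go on to regression.
- *The second-step regression is the correct analysis being withheld.* As worded it covers facility clustering and names no provider-level term, so it may need the same repair.
- *A stated aim is compromised.* The Aims section names modern contraceptive use and unintended pregnancy. Provider attitudes are not among the 15 secondary outcomes in Table 1.

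What the objection does not reach is the choice of Pearson chi-square for repeated answers and the significance gate. Both are written out, so neither is detail left for later.

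**Conclusion.** The point holds in limited form. Pearson chi-square is the wrong test for repeated categorical answers from the same providers, and the significance gate is unsound whichever first-step test is used. For a 15-point change from 50% with 60 pairs and correlation 0.5, the screen passes about 34% of real effects, where McNemar would pass 64% (56% exact), at a true type I error below 1%. In that case the observed change among passing items averages about 22 points, and still about 19 with a McNemar gate.

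These sizes rest on assumed correlations and effects, complete pairs and no facility clustering. Clustering of change could offset or reverse the conservatism. Whether the t-tests are affected cannot be told from the text. The consequence is confined to the ancillary provider-training evaluation; no primary or secondary client result depends on it. It is worth correcting because the remedy is simple and uses data already planned.

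**What to change.** - For the descriptive table, name paired tests: McNemar for binary items, Stuart-Maxwell or Bowker for items with more than two categories, and explicitly paired t-tests for scores.
- Delete the condition that an item must be significant before it is modelled.
- For every item or scale, fit a regression suited to the outcome, with survey occasion as a fixed effect and random effects for provider nested in facility, across all four surveys.
- Report the estimate and confidence interval for every item, whatever its p-value.

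The single mixed model is one acceptable route. The minimum is paired tests, no gate, and a provider-level term wherever a regression is fitted. The cost is a change of wording in the protocol or analysis plan and a little programming. No new data are needed, provided that the identifiers link each provider's surveys, which should be confirmed.
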